### Blinding

This is a single-blind feasibility RCT; all outcomes will be collected by a blinded outcome assessor. It is not possible to blind either participants or physiotherapy practitioners to treatment due to the interventions under investigation.

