**Methods/Design:**

This study was designed to test the feasibility of an assessor-blind randomised controlled trial which assess the effects on clinical outcomes and exercise adherence of adding manual auricular acupuncture to a personalised and supervised exercise programme (PEP) for CLBP. No sample size calculation has been carried out as this study aims to identify CLBP referral rates within the catchment area of the study site. The researchers aim to recruit four cohorts of n = 20 participants to facilitate a power analysis for a future randomised controlled trial. A computer generated random allocation sequence will be prepared centrally and used to allocate participants by cohort to one of the following interventions: 1) six weeks of PEP *plus *manual auricular acupuncture; 2) six weeks of PEP alone. Both groups will also complete a further six weeks of self-paced exercise with telephone follow-up support. In addition to a baseline and exit questionnaire at the beginning and end of the study, the following outcomes will be collected at baseline, and after 7, 13 and 25 weeks: pain frequency and bothersomeness, back-specific function, objective assessment and recall of physical activity, use of analgesia, perceived self-efficacy, fear avoidance beliefs, and beliefs about the consequences of back pain. Since this is a feasibility study, significance tests will not be presented, and treatment effects will be represented by point estimates and confidence intervals. For each outcome variable, analysis of covariance will be performed on the data, conditioning on the baseline value.

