#### Telephone helpline

At the end of the structured exercise ± manual auricular acupuncture treatments (week 7), participants will be advised to continue with daily self-directed exercise/activity as agreed with the therapist. A free telephone helpline will also be available three times per week for a two-hour period for a further six weeks for participants who feel that they need advice or support from the therapist, or to answer any other queries or concerns participants may have. Participants' use of this helpline will be closely monitored and calls recorded and at the end of this phase (week 13), each participant will receive a telephone follow-up call from their therapist to provide advice on exercises and functional activities as appropriate, to reinforce the value of exercise adherence, and if necessary to re-evaluate treatment goals.

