### Outcome measures

A number of outcome measures will be collected at week 1 (baseline), and week 7 (end of scheduled exercise ± manual AA) by a blinded assessor as part of the scheduled intervention, and by post at week 13 and at 6 months after initial randomisation (except for the Readiness to Change Questionnaire, the Holistic Complementary and Alternative Health Questionnaire and the Exit Questionnaire). The uptake of the free telephone advice and support service, available between weeks 8–13, will be monitored to establish the value of such a service in a future RCT. Participants in treatment group A will be asked to record in their daily activity logbook how often they manually stimulated the stud needles during the 48 hour treatment period, and all participants will also be asked to record any changes in their analgesic intake during the trial. All outcome measures data will be securely stored and analysed once the trial is complete. Treating physiotherapists will be made aware of the results of the Readiness to Change, Back Beliefs, Fear Avoidance Beliefs Questionnaires and the General Perceived Self-Efficacy Scale, in order to adapt the PEP accordingly.

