#### Visual Analogue Scale (VAS) (0–10 cm)

The VAS is widely used within the clinical setting, and demonstrates acceptable reliability, particularly when used with the same individual [28]. Since such a scale only assesses one dimension of pain, it is recommended that both the bothersomeness and intensity of pain are captured within the assessment, and an average score recorded [28,29]. Participants will be asked to rate their level of back pain and leg pain on average over the past week.

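### Assessor blinding is claimed for all outcomes, but week 13 and six-month data come by post and are mostly self-reported by unblinded participants; the week 13 questionnaire also has no fixed order relative to the therapist's call

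*Protocol article*

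**What the plan says.** The protocol article describes the design as assessor-blind (Abstract; Study design) and single-blind (Blinding). The Blinding section states that "all outcomes will be collected by a blinded outcome assessor", and continues: "It is not possible to blind either participants or physiotherapy practitioners to treatment due to the interventions under investigation".

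The schedule in the Abstract is that "the following outcomes will be collected at baseline, and after 7, 13 and 25 weeks". The Outcome measures section gives the mode of collection. At weeks 1 and 7 the data are collected "by a blinded assessor as part of the scheduled intervention". After that they are collected "by post at week 13 and at 6 months after initial randomisation".

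The Telephone helpline section covers the self-directed phase after week 7. It provides that "at the end of this phase (week 13), each participant will receive a telephone follow-up call from their therapist to provide advice on exercises". The call is also meant to encourage continued exercise and, where needed, to revisit goals.

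**The concern.** Blinding an assessor protects an outcome when the assessor observes, rates or elicits it. It does little for an outcome that participants rate themselves when they know their arm, and it cannot act at a time point where participant and assessor have no contact. If the Blinding section is taken at face value, a reader of the results will credit the effect estimates with a protection that most of them lack.

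The comparison is an open add-on: one arm receives an extra hands-on treatment and the other does not. Self-reports are exposed to response bias in that setting. The estimates will be used. Objective (vii) is to obtain a rough effect size, and the Discussion makes the case for a fully powered trial depend on seeing clinically important added effects of acupuncture.

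The timing at week 13 is a separate matter. The call is about exercise, adherence and goals. The questionnaires due in the same week ask about fear-avoidance, back beliefs, self-efficacy and recalled activity. If some people reply before the call and others after it, the week 13 value does not mean the same thing for everyone.

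**Working it through.** The plan gives no figure on this point, so the check sets the sections side by side.

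**Step 1. Who collects what, and when**

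| Time point | Mode (Outcome measures) | Blinded assessor named? | Therapist call (Telephone helpline) |
|---|---|---|---|
| Week 1 | Scheduled visit | Yes | No |
| Week 7 | Scheduled visit | Yes | No |
| Week 13 | Post | No | Yes, every participant |
| Week 25 (six months) | Post | No | No |

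An assessor is named at 2 of 4 time points. Of the 3 post-baseline time points, 1 has an assessor and 2 are postal. The word *all* in the Blinding section is not matched by the schedule.

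**Step 2. Who generates the data**

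The article's descriptions of the instruments give this division:

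- Reported by the participant: pain VAS ("Participants will be asked to rate their level of back pain and leg pain on average over the past week"), Oswestry, IPAQ recall, activity and analgesic logbook, the physical activity part of the FABQ, Back Beliefs, self-efficacy and EuroQol-5D.
- Recorded by a device: activPAL, worn for seven days at each time point.

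Eight listed instruments come from the participant's own report and one from a device. Since participants know their arm, the eight are unblinded at week 7 as well as at weeks 13 and 25. A blinded person who hands over a questionnaire does not blind the person who fills it in.

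**Step 3. Week 13**

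The call and the postal questionnaire carry the same week label, and neither section says which comes first. How far the order can matter depends on the recall period:

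- VAS and IPAQ look back over seven days. If a pack is completed *k* days after the call (*k* from 0 to 7), about *k* of the 7 recalled days follow the call. As an illustration, *k* = 0 gives 0 of 7 and *k* = 3 gives 3 of 7.
- The article states no recall period for the FABQ, Back Beliefs or self-efficacy scale. Answers to these could shift straight after the call.

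The exposure is therefore greatest for beliefs and self-efficacy, partial for recalled activity, and smaller for average pain over the past week. It concerns week 13 only: weeks 1 and 7 come before the call, and week 25 is 25 − 13 = 12 weeks after it for everyone.

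**The case against.** The strongest reply has four parts.

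- **Unblinded participants are disclosed.** The sentence after the blinding claim says so, and the trial is called single-blind. This stands: nothing is concealed. However, the article does not connect that admission with the fact that these same people supply most of the outcome data, and the word *all* remains wrong for the schedule as described.
- **A blinded person may handle the postal returns.** The article gives the mode but not who sends, receives or enters the packs, and a condensed article may leave that to the full protocol. This also stands. A reader might infer that no blinded person touches the postal data, and the document does not support that. But blind handling of returns would protect data processing, not the answers.
- **The call goes to both arms.** A reader might infer that it favours the acupuncture arm because the caller knows the allocation. The document gives no mechanism for this: the call is common to both arms, and the same therapists have already run six weeks of classes. What remains is a mixture of responses given before and after the call.
- **The study is small and exploratory.** No significance tests are planned and the effect size is meant to be crude. This limits the consequence but does not remove it, because piloting the procedures is itself an objective.

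A reader might also suppose that visible ear plasters unmask the week 7 assessor for a whole class. The Auricular acupuncture section has the needles removed after 48 hours, and nothing shows that the week 7 assessment falls inside that period. The point is conjecture.

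**Conclusion.** The concern holds in limited form. The Blinding section claims more than the Outcome measures section provides: assessor contact is stated for 1 of 3 follow-ups, and most outcomes other than activPAL are self-reported by people who know their arm. The assessor-blind label overstates protection against response bias. Separately, the week 13 questionnaire and the therapist's call have no fixed order, so week 13 answers on beliefs, self-efficacy and activity can mix two conditions.

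It is tempting to express the possible bias in Oswestry points and compare it with the 4% important change that the article cites. The article gives neither a standard deviation nor any basis for a size of bias, so such a number would rest wholly on assumption, and none is offered here. Nor does it follow that activity conclusions should rest on activPAL alone. Whether the device is a useful outcome tool is one of the study's own questions.

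The verdict assumes that the article describes the collection modes completely. If the full protocol provides for blind handling of postal returns or activPAL data, the claim may be extended to those steps. It still would not cover the self-reports.

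**What to change.** 1. Restate the Blinding section. Claim assessor blinding only for the week 1 and week 7 assessments, and for activPAL handling and processing of postal returns if these are in fact done blind.
2. State that participant-reported outcomes are unblinded at all time points, and interpret the crude effect sizes with that in mind when planning the main trial.
3. Time the week 13 pack so that it is completed before the week 13 call, and record the completion date and the call date. The call itself need not change.
4. Optionally, have the week 7 assessor record a guess of the arm, which would show how well the blinding held where it applies.

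The cost is a change of wording, a slightly earlier mailing and two recorded dates. The one real drawback is that the stated blinding becomes less favourable.

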### Qualitative assessment of this feasibility study

This will be conducted at the end of the treatment sessions (structured exercise ± manual auricular acupuncture) either at week 13 or week 25, depending on availability of the participants, in an attempt to improve the design, implementation and acceptability of the main RCT.

#### Participant Focus Groups

Participants will be invited to attend a focus group discussion. Each group will consist of a maximum of eight participants and will take place over a two-hour period. A 'clue and cue process', using a checklist of topics, will be used to ensure that the same basic areas are covered, but allowing any issues of importance to the participants to emerge. The main areas to be explored will be participants' interpretation of study information and documentation, their experiences, expectations and satisfaction with the programme of care, and acceptability of being involved in the trial. Sessions will be moderated by an experienced focus group moderator, audio-tape recorded, and field notes will be prepared by another member of the research team, not involved in the day-to-day running of the trial. Interviews will be transcribed, and interpretation, synthesis and data reduction undertaken independently by two members of the research team.

#### General Practice Interviews

An independent interviewer will also conduct one to one interviews with general practitioners and other staff, within each participating general practice, to explore strategies to improve referral and recruitment to the trial, and to assess their views of the overall value of the study to the National Health Service. Interviews will be audiotape recorded, transcribed and analysed as for the focus groups above.

### Statistical methods

Since this is a feasibility study, significance tests will not be performed or reported, and treatment effects will be represented by point estimates and confidence intervals. For each outcome variable ANCOVA will be performed on the data, conditioning on the baseline value. Trends over time and time-by-treatment interactions will be explored using repeated measures ANOVA. The influence of treatment preference on outcomes will also be explored. For all analyses, the residuals will be examined for evidence of non-normality. If substantial evidence of non-normality is found, appropriate alternative (non-parametric) tests will be applied, and specified as the primary analysis method in the main study. The cluster randomised nature of the design will be accounted for in the analysis by fitting a mixed effects model. Monthly recruitment rates and ratio of number screened: number enrolled will be tabulated. This information will be used to help select the recruitment period and number of centres for the main RCT. The assessment of participant satisfaction will be tabulated, as will any recorded difficulties experienced by the participants or therapists. This information may be used to modify the interventions used in the main RCT. If analgesic use differs substantially between the two groups, consideration will be given to using this as a primary outcome variable in the main RCT.

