### Sample size

No sample size calculation has been carried out as this study aims to identify the referral rates of CLBP participants within the catchment area of the study site. Recruitment will be on a consecutive basis from participating practices, physiotherapy waiting lists and the general public, and will enable the researchers to estimate expected recruitment rates from each of these sources for the main RCT. The researchers aim to enrol eight cohorts of participants, each containing a maximum of n = 10 participants (total n = 80 participants), with randomisation to treatment taking place by cohort. Based on the results of previous trials investigating exercise or acupuncture for LBP, a 30% drop-out rate is anticipated between the beginning of treatment and the follow-up, so it is anticipated that n = 56 participants will complete the trial. The trial statistician is satisfied that this sample size will be sufficient to refine the study protocol, perform a power analysis, and establish the number of participants needed for the main RCT.

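### The plan names ANCOVA, repeated measures ANOVA and a mixed effects model without saying which supplies the reported intervals; only the last is said to account for cohort randomisation

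*Protocol article*

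**What the plan says.** Treatment is allocated to whole cohorts: the Sample size section of the protocol article has "with randomisation to treatment taking place by cohort", and the Randomisation section agrees. The Sample size section plans eight cohorts of at most 10 people, 80 in all. The Abstract gives a different structure for the same total: "The researchers aim to recruit four cohorts of n = 20 participants".

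The Statistical methods section excludes significance tests, so treatment effects are reported only as point estimates with confidence intervals. It then names three methods:

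- "For each outcome variable ANCOVA will be performed on the data, conditioning on the baseline value".
- For the course of outcomes across the follow-up visits: "Trends over time and time-by-treatment interactions will be explored using repeated measures ANOVA".
- After the sentences on treatment preference and residual checks: "The cluster randomised nature of the design will be accounted for in the analysis by fitting a mixed effects model".

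The section does not link the third method to the first two. The Abstract mentions only the ANCOVA.

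On losses, the Sample size section says "a 30% drop-out rate is anticipated between the beginning of treatment and the follow-up", and so "it is anticipated that n = 56 participants will complete the trial". Follow-up is at weeks 7, 13 and 25. The Outcome measures section has week 7 collected by the blinded assessor and the two later time points by post.

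**The concern.** In their standard form, ANCOVA and repeated measures ANOVA treat participants as independent. When whole cohorts are allocated, people in the same cohort share a class and a period, and any similarity this creates adds variance to the treatment contrast that a participant-level standard error does not see. An analyst following the text literally could report ANCOVA intervals and fit the mixed model only as a companion analysis.

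Classical repeated measures ANOVA also needs every visit from every participant. Someone seen at week 7 who did not return a later postal questionnaire would drop out of it altogether.

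The intervals matter because they are the only quantitative treatment result. They inform the effect-size objective, the power analysis for the main trial and, according to the Discussion, the decision whether a main trial is worthwhile. If the three methods give different intervals, the plan does not say which one counts.

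**Working it through.** **1. The plan's own figures.** 8 × 10 = 80 enrolled and 80 × (1 − 0.30) = 56 completers, as stated. Completers per cohort: 56 / 8 = 7. Not completing: 80 − 56 = 24. The Abstract's 4 × 20 also gives 80.

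**2. Assumed inputs.** The documents give no ICC and no confidence level. I take a 95% level and ICCs of 0, 0.01, 0.05 and 0.10. Cohort size m is 10 (all enrolled) or 7 (completers).

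**3. Interval width.** The design effect is 1 + (m − 1) × ICC. A cohort-level interval uses t on K − 2 degrees of freedom, where K is the number of cohorts. For K = 8, t(6) = 2.447. At equal standard error this is 1.229 times the participant-level limit for m = 10 and 1.220 times for m = 7. The ratio of cohort-level to participant-level width is that factor times the square root of the design effect.

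- m = 10: 1.229 × √1.09 = 1.28 at ICC 0.01; 1.229 × √1.45 = 1.48 at 0.05; 1.229 × √1.90 = 1.69 at 0.10.
- m = 7: 1.220 × √1.06 = 1.26; 1.220 × √1.30 = 1.39; 1.220 × √1.60 = 1.54.

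**4. Coverage of nominal 95% intervals.** This was simulated with 40,000 runs per setting, balanced cohorts, no true effect and no baseline covariate. The ICC is therefore best read as the value left after baseline adjustment. The simulation error near 95% is √(0.95 × 0.05 / 40,000) = 0.0011, or about 0.1 percentage point.

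| Method | K × m | ICC 0 | 0.01 | 0.05 | 0.10 |
|---|---|---|---|---|---|
| Participant level | 8 × 10 | 95.0 | 93.9 | 89.6 | 84.4 |
| Participant level | 8 × 7 | 95.0 | 94.5 | 91.5 | 87.8 |
| REML mixed model, ±1.96 | 8 × 10 | 95.8 | 95.2 | 93.3 | 92.1 |
| REML mixed model, ±1.96 | 8 × 7 | 95.7 | 95.5 | 93.9 | 92.5 |
| REML mixed model, t(6) | 8 × 10 | 98.8 | 98.5 | 97.4 | 96.6 |
| Participant level | 4 × 20 | 95.0 | 92.9 | 83.5 | 74.4 |
| REML mixed model, ±1.96 | 4 × 20 | 96.0 | 94.7 | 90.1 | 87.0 |

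Cohort means with t on K − 2 degrees of freedom covered 95% at every ICC tried, for both structures.

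**5. Number of cohorts.** Eight cohorts give 8 − 2 = 6 degrees of freedom (t = 2.447). Four give 4 − 2 = 2 (t = 4.303). The two statements therefore imply very different intervals.

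**6. Missing visits.** If the 24 expected dropouts each miss at least one visit, a complete-case repeated measures ANOVA loses all 24, including any week 7 or week 13 values they supplied. A likelihood-based mixed model keeps those values.

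**7. Attendance.** The Education component section records adherence to the supervised classes as the number of sessions attended. That count has no pre-treatment value, so an ANCOVA conditioning on baseline cannot be applied to it.

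**The case against.** The strongest reply is that the plan already deals with clustering. The mixed-model sentence comes after the other methods and speaks of the analysis as a whole, so it can be read as fitting the ANCOVA and the time terms within a model that carries a cohort effect. On that reading the participant-level coverage figures describe an analysis nobody intends. A normal-based mixed model with eight cohorts loses only about 1 to 3 points at ICC 0.05 to 0.10 and nothing at 0.01 or below. The repeated measures ANOVA is exploratory, and the effect-size objective asks only for a rough figure.

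Much of this stands. A reader might infer that the plan ignores clustering, that its intervals are certainly too narrow, or that dropouts' data will be discarded. The document supports none of these as fact. It commits to accounting for the cohort design and states no complete-case rule. ANCOVA run separately at each visit would keep the week 7 values of people lost later, so a completers-only week 7 effect is not what the plan describes.

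Nor is the absence of a degrees-of-freedom method an error in itself. That detail is commonly left to a full protocol or analysis plan, which is not shown here. Session attendance is a minor point: it is not among the listed outcome instruments, and activity outside class is also measured.

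What the reply does not remove is that the text permits either reading, and that classical repeated measures ANOVA is explicitly named although it suits neither cohort allocation nor 30% dropout.

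**Conclusion.** The concern holds in conditional form. The plan does not say which of its three methods supplies the reported intervals. If a participant-level method does, nominal 95% intervals with eight cohorts of 7 to 10 cover about 90 to 92% at ICC 0.05 and 84 to 88% at ICC 0.10. The shortfall is about 1 point or less at 0.01, and there is none at 0. If the mixed model does, the shortfall with eight cohorts is small. Four cohorts would make both cases worse.

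Separately, the named repeated measures ANOVA in its classical form could omit the interim data of up to 24 of 80 participants from the time-by-treatment exploration.

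These sizes rest on assumed ICCs, a 95% level, equal cohort sizes and no baseline covariate. The upper figure of 24 assumes that every expected dropout misses a visit.

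**What to change.** Replace the repeated measures ANOVA and the stand-alone ANCOVA with one mixed model per repeated outcome. It should take weeks 7, 13 and 25 together, use all available visits, and include the baseline value as covariate, treatment by visit, and random effects for cohort and participant. State that this model supplies every treatment estimate and interval. Use cohort-level small-sample degrees of freedom: Kenward-Roger, or an analysis of adjusted cohort means with t on 6 degrees of freedom for eight cohorts.

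Reconcile the cohort numbers in the Abstract and the Sample size section, since they set the degrees of freedom at 6 or 2. Report session attendance as a difference in cohort means, with an interval on the same degrees of freedom.

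The cost is wording and somewhat wider intervals: up to about 25% wider than normal-based ones with eight cohorts (2.447 / 1.960 = 1.25). Applying t(6) to a REML fit is somewhat conservative at low ICC (98.5% coverage at 0.01 with cohorts of 10). Adjusted cohort means should largely avoid this, as unadjusted cohort means held 95% throughout the simulation.

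### The non-normality fallback switches to non-parametric tests in a paragraph that rules out testing, and commits the main trial to them as its primary analysis

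*Protocol article*

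**What the plan says.** All of the relevant commitments stand in one paragraph of the protocol article, Statistical methods:

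- **No testing, estimates only:** "significance tests will not be performed or reported, and treatment effects will be represented by point estimates and confidence intervals". The abstract (Methods/Design) gives nearly the same rule: "significance tests will not be presented, and treatment effects will be represented by point estimates and confidence intervals".
- **Baseline adjustment:** "For each outcome variable ANCOVA will be performed on the data, conditioning on the baseline value".
- **Trigger for the fallback:** "For all analyses, the residuals will be examined for evidence of non-normality".
- **Fallback and carry-over:** if that evidence is substantial, "appropriate alternative (non-parametric) tests will be applied, and specified as the primary analysis method in the main study".
- **Clustering, in the next sentence:** "The cluster randomised nature of the design will be accounted for in the analysis by fitting a mixed effects model".

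On the number of randomised units, Sample size gives "eight cohorts of participants, each containing a maximum of n = 10 participants (total n = 80 participants), with randomisation to treatment taking place by cohort". The abstract gives "four cohorts of n = 20 participants to facilitate a power analysis for a future randomised controlled trial".

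**The concern.** There are two problems in the text itself.

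First, the fallback is to tests, in a paragraph that says tests will be neither performed nor reported. An analyst who meets skewed residuals cannot follow both instructions. The study needs estimates: the last objective under Aim and Objectives is a crude effect size for each treatment package, and Sample size says the data will support a power analysis. A test result alone supplies neither.

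Second, once the check triggers, the sentence sets the main trial's primary analysis. The purpose of this study is to design that trial, so the choice is one of its products. A residual check in a small sample is a weak basis for it, because inference on means depends less on normal residuals as the sample grows.

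A third point follows from these. The paragraph promises conditioning on baseline and allowance for cohort, and it does not say how either would survive the switch. The outcomes include analgesic intake and recalled activity time, which are often skewed, so the trigger is not remote. The same paragraph names analgesic use as a possible primary outcome for the main trial.

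**Working it through.** **1. The plan's own figures.** 8 cohorts × 10 = 80 enrolled; 80 × (1 − 0.30) = 56 completers. Both agree with Sample size. Spread evenly, 56 / 8 = 7 completers per cohort. The abstract's 4 × 20 also gives 80, but with half as many randomised units.

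**2. The commitments set against the fallback.**

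| Commitment in Statistical methods | Usual two-sample rank test |
|---|---|
| No significance tests | Is a significance test |
| Point estimate and interval | Not part of the test; needs a further step |
| Conditions on baseline | No |
| Allows for cohort | No; treats participants as independent |
| Mixed effects model | As ordinarily fitted, parametric, and rests on the residual assumption that has just failed |

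The first row is a contradiction on the face of the text. The other rows depend on which method is chosen, and none is named.

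**3. Size of the clustering risk if an ordinary Mann-Whitney test were used.** Assumptions: 4 v 4 cohorts, no treatment effect, nominal two-sided 5%, 8,000 simulated trials per setting (Monte Carlo standard error near 5%: √(0.05 × 0.95 / 8000) ≈ 0.24 percentage points). The ICCs are assumed, because the document gives none. Design effect = 1 + (m − 1) × ICC. Data were generated as normal. Ranks do not change under a monotone transformation, so the same rates apply to a skewed outcome that has this structure on, say, the log scale.

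| ICC | Design effect, m = 7 | Type I error, m = 7 | Design effect, m = 10 | Type I error, m = 10 |
|---|---|---|---|---|
| 0 | 1.00 | 4.6% | 1.00 | 5.3% |
| 0.01 | 1.06 | 5.3% | 1.09 | 5.8% |
| 0.05 | 1.30 | 7.9% | 1.45 | 10.4% |
| 0.10 | 1.60 | 11.5% | 1.90 | 15.2% |

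A t test on the eight cohort means, run on the same simulated data, stayed between 4.6% and 5.5% throughout.

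**4. Cost of losing baseline, if it were lost.** Adjustment multiplies the variance by 1 − r², so dropping it inflates the variance by 1 / (1 − r²). With assumed r = 0.5 this is 1 / 0.75 = 1.33; with r = 0.7 it is 1 / 0.51 = 1.96.

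**5. A rank test at cohort level.** This would respect the randomisation but is very coarse. The smallest two-sided p-value is 2 / C(8,4) = 2 / 70 = 0.029 with 4 v 4 cohorts, and 2 / C(4,2) = 2 / 6 = 0.333 with 2 v 2. The two cohort counts in the article therefore decide whether this route is usable at all.

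**The case against.** The strongest defence is that the article names no test and says only that the alternative will be appropriate. Rank ANCOVA keeps baseline, cluster-adjusted and cohort-level rank methods keep cohort, and rank methods can be made to yield an estimate with an interval. The sentence after the fallback applies a mixed effects model to the analysis without exempting the fallback. Which method is used, and how it yields an interval, is normally left to an analysis plan, and none is shown here. The fallback is conditional, and effect size is the last of seven objectives and described as crude.

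Much of this stands. A reader might infer that the plan discards baseline and cohort whenever residuals are skewed, that it would report a bare p-value, or that the main trial will inherit an unadjusted analysis that ignores clustering. The document supports none of these. It states no such intention, it gives no outcome distributions that would show the trigger being met, and it does not fix the main trial's unit of randomisation.

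Two things do not yield to the defence. The conflict between excluding tests and prescribing them is in the text and is not a matter of omitted detail. So is the commitment of the main trial to the fallback method. The mixed-model sentence does not reconcile the paragraph either, because that model as ordinarily fitted cannot be combined with the usual rank tests.

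**Conclusion.** The point holds as an internal contradiction and a poorly founded carry-over. The paragraph excludes significance tests, then prescribes them under non-normality, and makes them the main trial's primary method on the strength of a residual check in about 56 completers. The fallback is compatible with the promised baseline adjustment, clustering and interval only if a particular method is specified.

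The numerical risk is conditional on an ordinary Mann-Whitney test that ignores cohort, with eight cohorts split equally. Type I error is then about 5-6% at ICC 0.01, 8-10% at 0.05 and 11-15% at 0.10. At the lowest ICC the harm is slight. These figures, and the 33-96% variance inflation from losing baseline, rest on assumed ICCs and correlations. They do not describe what the plan says it will do.

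Severity is moderate: this is a conditional rule in a feasibility study, but it bears on what the study is meant to deliver.

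**What to change.** Replace the fallback sentence with a rule that keeps estimation. For outcomes with markedly non-normal residuals, report a baseline-adjusted, cohort-respecting estimate with a confidence interval. Two workable forms are:

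- the same mixed effects model on a transformed outcome (for example log), with back-transformed estimates and intervals; or
- baseline-adjusted cohort means compared with a t interval on number of cohorts minus 2 degrees of freedom. That is 8 − 2 = 6 if the cohorts are as in Sample size, and 4 − 2 = 2 if they are as in the abstract.

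Reconcile the two cohort counts before relying on the second form. Add a sentence saying that the pilot residual check informs the choice of the main trial's primary analysis but does not fix it.

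The cost is a few sentences of wording and no extra data. On the log scale the effect is reported as a ratio and not as a raw difference, and cohort-level intervals will be wider.
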